| \| **Primary Objective** \| **Primary Endpoint** \| \| --- \| --- \| \| Compare the efficacy of ruxolitinib in combination with corticosteroids versus corticosteroids in terms of overall response rate (ORR) at Day 28 in subjects with acute graft-versus-host disease (acute GVHD). \| ORR at Day28, defined as the proportion of participants demonstrating a complete response (CR), or partial response (PR) \| \| **Secondary Objective** \| **Secondary Endpoints** \| \| Compare additional response and longer-term efficacy outcomes between treatment cohorts. \| Durable ORR at Day56, defined as the proportion of patients in each arm whose response on day 28 lasts until day 56 after randomization. \| \| DOR at Month 6 for responders will be calculated. The DOR is defined from the time of the onset of response to loss of response. Subjects who died or discontinued will be censored at the  death date or the previous assessment. \| \| Response duration, defined as the time from the first response to the first recurrence/progression of acute GVHD or additional immunosuppressants for GVHD. \| \| NRM at Month 24, defined as the time from enrollment to death due to any causes other than hematologic disease relapse. \| \| Cumulative incidence of relapse (CIR) at Month 24, defined as the proportion of subjects whose underlying hematologic disease relapses. \| \| Disease-free survival (DFS) at Month 24, defined as the time from enrollment to relapse of primary disease or death from any causes, whichever occurred first. \| \| Failure-free survival (FFS) at Month 24, defined as the time from randomization to disease relapse or progression, non-relapse mortality, or the addition of new therapy for acute GVHD. \| \| Overall survival (OS) at Month 24, defined as the time from randomization to death due to any causes. \| \| Assess the incidence and severity of adverse events (AEs) and serious adverse events. \| Clinical safety data (eg, AEs, infections) will be tabulated and listed. \| \| Evaluate the use and discontinuation of  corticosteroids. \| Average and cumulative corticosteroid dose at Days 365; \| \| Evaluate the use and discontinuation of  immunosuppressive medications. \| Proportion of subjects who discontinue immunosuppressive medications at Days365. \| \| Evaluate the incidence of recurrent acute GVHD \| Incidence rate of recurrent acute GVHD through Month 24. \| \| Evaluate the incidence of cGVHD. \| Incidence rate of cGVHD at Month 24. \| \| **Overall Study Design:**  This trial is an open-label, multicenter, prospective randomized two-arm phase II study comparing the efficacy and safety of ruxolitinib plus methylprednisolone (1 mg/kg) vs. methylprednisolone (2 mg/kg) alone. The biomarkers of acute GVHD, such as sST2, sTNFR1, IL-6, IL-8, and REG3α will be tested at acute GVHD onset. Patients with newly diagnosed intermediate-risk or high-risk acute GVHD, as defined by Minnesota acute GVHD risk score and the biomarker score will be included. The treatment efficacy will be evaluated with respect to the level of biomarkers and clinical manifestations. Written informed consent must be obtained from the patients before enrollment in the study. The consent form and related materials are available from the corresponding author on request.  **Study Population:**  Eligible patients with intermediate-risk or high-risk acute GVHD graded according to the modified Glucksberg criteria, Minnesota acute GVHD risk score and the biomarker score and untreated with systemic acute GVHD therapy will be enrolled in this study.  **Key Inclusion Criteria:**   - Male or female, 14 to 65 years old. - Have undergone first allogeneic hematopoietic stem cell transplantation (allo-HSCT) from any donor source using bone marrow, peripheral blood stem cells, or cord blood for hematologic malignancies. - Develop a de novo acute GVHD, defined as intermediate- or high-risk using the Minnesota acute GVHD risk score and MAGIC biomarker algorithm.   **Key Exclusion Criteria:**   - Has received more than one allogeneic stem cell transplant. - Female patients with pregnant or breast-feeding. - Has Acquired Immune Deficiency Syndrome (AIDS), or hepatitis B/C infection, uncontrolled bacterial, fungal, or viral infections. - Allergies to ruxolitinib. - Vital organ dysfunction unrelated to GVHD, including persistent bilirubin abnormalities or severe heart and respiratory diseases. - Relapse of the primary disease or graft rejection after transplantation. - Presence of GVHD overlap syndrome. - Presence of cGVHD or associated clinical signs or DLI-induced acute GVHD or interferon. - Previous history of JAK1/2 inhibitor treatment after transplantation, except JAK inhibitors administered before the transplantation. - absolute neutrophil count (ANC) <0.5×10^9^/L or platelet count (PLT) < 20×10^9^/L - Serum creatinine > 2.0 mg/dL or creatinine clearance < 40 mL/min measured or calculated by Cockroft-Gault equation. - Patients with poor compliance should not be included in the study based on the judgment of the research team, for example if they refused to take medicine at will many times during the previous treatment.   **Study Drug, Dosage, and Mode of Administration:**  **Ruxolitinib plus corticosteroids treatment (ruxolitinib group):**  The initial dose of methylprednisolone is 1 mg/kg/day intravenously given in this arm for at least 7 days. The dosage of ruxolitinib is 5 mg PO QD. CSA will be administered intravenously at a dose of 2 mg/kg twice daily, targeting minimum concentration levels of 150–250 ng/mL. If GVHD response to treatment is assessed as PR/CR at 7 days, methylprednisolone will be tapered, followed by reduction and discontinuation of CSA and then ruxolitinib. The reduction of the methylprednisolone in the ruxolitinib group is gradual, suggesting it be tapered off over 6 weeks as follows: dosage reduced to 0.6 mg/kg/day, 0.4 mg/kg/day, 0.3 mg/kg/day, 0.25 mg/kg/day, and 0.18 mg/kg every 5 days, followed by 0.1 mg/kg/day at week 4, 0.1 mg/kg every other day after 5 days and stopped at week 6. After steroid discontinuation and CR or stable PR maintained for 6 weeks, CSA is tapered over 60 days. After CSA discontinuation and no presence of recurrent GVHD, ruxolitinib is tapered off over 90 days, which is totally maintained for approximately 6 months.  **Corticosteroid treatment (corticosteroids group):**  The initial dose of methylprednisolone is 2 mg/kg/day given twice daily for at least 7 days and then reduced. The dosage of methylprednisolone in the corticosteroids group is decreased gradually after CR and tapered off over 10 weeks as the following: dosage reduced to 1 mg/kg/day to 0.6 mg/kg/day, 0.4 mg/kg/day, 0.3 mg/kg/day, 0.25 mg/kg/day, and 0.18 mg/kg every 7 days, and then 0.1 mg/kg/day at week 4, 0.1 mg/kg every other day after 5 days, and stopped at week 10. CsA was administered intravenously at a dose of 2 mg/kg twice daily, targeting minimum concentration levels of 150–250 ng/mL. The recommended duration of CsA is 6 months.  In both arms, for refractory acute GVHD, i.e., the progression of GVHD after 3 days of therapy, no improvement within 7 days, or no CR after 14 days of therapy, the second-line therapy will be started. For refractory acute GVHD or recurrent acute GVHD, basiliximab may be used as second-line therapy, and other alternative drugs included methotrexate or mesenchymal stem cells may be used at the researcher’s decision. For refractory acute GVHD, methylprednisolone is discontinued and CsA is continued in both arms. Prolonged maintenance of ruxolitinib is used in the ruxolitinib group. A standardized follow-up booklet is given to each enrolled patient for recording the dose, frequency, and administration method of the drugs. **Estimated Duration of Participation:** Subject participation is expected to average 24 months, which includes the following:   - A screening period lasting up to 28 days. - A treatment period lasting as long as the subject is benefiting from treatment. - A safety follow-up period lasting 180 days after treatment ends. - A survival follow-up period lasting until death or study withdrawal. \| \| \| **Estimated Number of Subjects:** 198 subjects. \| \| \| **Principal Coordinating Investigator:** [name] \| \| \| **Statistical Methods:**  The sample size is calculated according to the primary endpoint (ORR) of the study. Based on our published phase I study of 32 acute GVHD patients who received steroids as first-line therapy, an expected proportion of 55% for the patients treated with corticosteroids only was established. Based on our published data of patients with acute GVHD grade I–IV who received steroid-ruxolitinib (5 mg/day) as first-line therapy, the ORR was 82.05%. Patients with acute GVHD grade I were also included in the phase I analysis. Thus, an expected proportion of 75% for the patients treated with steroid-ruxolitinib (5mg/day) was established. This study is planned to detect a response difference between treatment arms at a two-sided significance level α=5% with a power of 1-β=80%. The sample size was estimated using PASS software based on the primary endpoint (ORR). Allowing a withdrawal rate of 10%, 198 patients (99/group) will be required.  Continuous data are described as median with interquartile range (IQR) or mean and standard deviation (SD) according to the normality of distribution. The categorical data are described as n (%). The ORR was calculated with its 95% confidence interval (CI) and compared by the stratified Cochran–Mantel–Haenszel test. Additionally, a logistic regression model, which included aGVHD risk (high vs. intermediate), and disease status before transplantation (CR vs. no CR) as covariates, was established to explore the association between treatment and ORR on day 28. Post-hoc subgroup analysis was performed by biomarker risk, age and GVHD grade, although these were not prespecified in the protocol. The cumulative incidence of recurrent aGVHD was analysed using the Fine and Gray test in a competing risk framework. The Kaplan–Meier method was used to estimate the ORR on day 56, OS, DFS, and FFS, and the log-rank test was used to evaluate the difference between the groups. The cumulative incidence rates of NRM and relapse were estimated using a competing risk model and compared using the Fine and Gray test. A Cox proportional hazard regression model was used for multivariable regression analysis for OS and DFS. Multivariable regression analysis was performed for NRM using the Fine–Gray proportional hazard regression for competing events. The following variables were included in the univariable analysis: primary disease, cytogenetic risk, age and gender of the donor and recipient, source of graft, treatment arm, aGVHD risk, and disease status before transplantation. Variables with P<0.1 in univariate analysis or variables known to influence the outcomes were included in the multivariable analysis. Competing events were defined as follows: for GVHD, death without the event; for relapse, death without relapse; and for NRM, relapse. Any difference for which the two-sided P<0.05 was considered statistically significant. All analyses were carried out using SPSS 22.0 software (IBM Corporation, Armonk, NY, USA) or R version 4.1.2 (www.cran.r-project.org). All statistical analyses were based on the intend to treat set. \| \| | |

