## 4.4. Randomization

The eligibility of patients is determined by study site staff. Then, the participants who meet the enrollment criteria will be randomized to receive one of the two treatments in a 1:1 ratio and stratified by disease status before transplantation (complete remission vs. non- complete-remission) and risk of acute GVHD (intermediate-risk vs. high-risk). Stratified permuted block randomization lists will be used to generate the stratified randomization. Randomization is implemented through an interactive web-based response system independent of study site staff and investigators. The codes are generated independently of the study by a statistician. The next assignment in the random sequence remained concealed because the treatment was assigned remotely. Treatment allocations are not masked to investigators or participants as CSA and methylprednisolone dosage are different between the two groups. The study staff who conducted the data analysis and assessments of outcomes will be masked for treatment allocations.

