### 8.3.2. Secondary Analyses

The estimated rates with two-sided 95% confidence intervals (CIs) are used for secondary endpoints (proportion of CR patients and patients who stopped treatment). The ORR on day 28 is calculated with its 95% CI. Kaplan–Meier method is used to estimate the DOR, OS, and DFS, and the log-rank test is used to evaluate the difference between the groups ^[21]^. The cumulative incidence of NRM and relapse is estimated using a competing risk model and compared using the Fine and Gray test. The Cox proportional hazard regression model is used for multivariable regression analysis for OS and DFS. The multivariable regression analysis for NRM is performed using the Fine–Gray proportional hazard regression for competing events. Potential risk factors considered in the regression analysis include primary disease, cytogenetic risk, age and gender of the donor and recipient, graft source, treatment arm, acute GVHD risk, and disease status before transplantation. The cumulative incidence of recurrent acute GVHD is analyzed using the Fine and Gray test in a competing risk framework. The threshold for statistical significance is set at 0.05, and all tests are two-sided. All analyses are carried out using SPSS 22.0 software (IBM Corporation, Armonk, NY, USA) and R version 4.1.2 (www.cran.r-project.org). The treatment-induced differences in OS and DFS will be based on the Cox proportional hazard regression model. The reported treatment difference in NRM and relapse will be based on the multivariate analysis using Fine–Gray proportional hazard regression.

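### The only tests named for FFS, DOR and recurrent acute GVHD leave out the two randomisation factors that the Day-28 ORR analyses use; adding them is a free improvement

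*Protocol*

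**What the plan says.** **Randomisation.** Section 4.4 of the protocol allocates patients 1:1, "stratified by disease status before transplantation (complete remission vs. non- complete-remission) and risk of acute GVHD (intermediate-risk vs. high-risk", and adds that "Stratified permuted block randomization lists will be used to generate the stratified randomization". Two factors with two levels each give four strata. The block size is not stated.

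**Primary endpoint.** Both factors are used for Day-28 ORR. The Synopsis names a stratified Cochran–Mantel–Haenszel test, and Section 8.3.1 a logistic model with both factors as covariates.

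**Secondary endpoints.** No strata are named for any between-arm test:
- DOR, OS and DFS (Section 8.3.2): "Kaplan–Meier method is used to estimate the DOR, OS, and DFS, and the log-rank test is used to evaluate the difference between the groups".
- FFS (Synopsis only; it does not appear in Section 8.3.2): "The Kaplan–Meier method was used to estimate the ORR on day 56, OS, DFS, and FFS, and the log-rank test was used".
- NRM and relapse (Section 8.3.2): "The cumulative incidence of NRM and relapse is estimated using a competing risk model and compared using the Fine and Gray test".
- Recurrent acute GVHD (Section 8.3.2): "The cumulative incidence of recurrent acute GVHD is analyzed using the Fine and Gray test in a competing risk framework".

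**Regression models.** Section 8.3.2 bases the treatment difference on Cox regression for OS and DFS, and on multivariable Fine–Gray regression for NRM and relapse. Acute GVHD risk and disease status are listed there as candidate covariates. Under the Synopsis rule a variable enters if its univariable P is below 0.1 or if it is known to influence the outcome. No model is named for FFS, DOR or recurrent acute GVHD.

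**The concern.** Blocking within strata makes the arms nearly equal on the stratification factors. If those factors predict outcome, the treatment contrast varies less from trial to trial than an unstratified test assumes. That test then rejects less often than its nominal level under the null, and less often than it could when treatment works. Section 1.2 gives reason to expect some prognostic effect, since it reports that the biomarker risk groups differ in NRM.

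What is at stake is power on secondary endpoints in a trial sized for ORR alone. FFS, DOR and recurrent acute GVHD are the most exposed, because the plain test is the only comparison the protocol gives them.

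**Working it through.** **1. The plan's own figure.** Section 8.1 gives 55% against 75% ORR, two-sided 5%, 80% power, 10% withdrawal and 198 patients. With pooled variance and no continuity correction,

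n per arm = [1.96·√(2·0.65·0.35) + 0.8416·√(0.55·0.45 + 0.75·0.25)]² / 0.20² = (1.322 + 0.555)² / 0.04 ≈ 88.1, so 89.

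89 / 0.90 = 98.9, so 99 per arm and 198 in total. This reproduces, and it fixes N. The protocol gives no event count or power for any time-to-event endpoint.

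**2. The statistic.** Z = U/√V, with U = Σ(a − p) and V = Σp(1 − p) over events. Here a is 1 if the patient with the event is in the experimental arm, and p is the share of the risk set in that arm. The unstratified test uses one risk set. The stratified test forms U and V within each of the four strata and adds them. Reject if |Z| > 1.96. For the Fine and Gray case, patients with a competing event stay in the risk set to 24 months (administrative censoring only).

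**3. Inputs.**
- From the protocol: N = 198, 1:1, permuted blocks in four strata, two-sided 5%.
- Assumed: blocks of 4, 50% high-risk, 30% not in complete remission, about 50% control events by 24 months, treatment hazard ratio 0.6, stratum hazard ratios from 1 to 3 per factor, and analysis of all randomised patients.
- For recurrent acute GVHD the Synopsis horizon of 24 months is used; Section 2 gives 12.
- Runs: 6,000 under the null and 4,000 under the alternative. Monte Carlo standard errors are about √(0.05·0.95/6000) = 0.3 points and √(0.6·0.4/4000) = 0.8 points.

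**4. Results, unstratified vs stratified.** The first column gives the stratum hazard ratios for GVHD risk and disease status.

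| Stratum HRs | Log-rank type I error | Log-rank power | Loss (points) | Fine and Gray type I error | Fine and Gray power | Loss (points) |
|---|---|---|---|---|---|---|
| 1, 1 | 4.9% vs 4.8% | 64% vs 64% | −0.3 | 5.5% vs 5.4% | 57% vs 57% | <0.1 |
| 1.5, 1.5 | 4.8% vs 5.1% | 62% vs 63% | 1.4 | 4.6% vs 5.2% | 57% vs 57% | 0.5 |
| 2, 2 | 3.7% vs 4.6% | 59% vs 63% | 4.1 | 3.7% vs 4.6% | 53% vs 57% | 4.0 |
| 3, 2 | 3.3% vs 5.2% | 55% vs 63% | 8.1 | 3.1% vs 4.9% | 50% vs 57% | 6.9 |
| 3, 3 | 2.8% vs 4.9% | 51% vs 64% | 12.7 | 3.2% vs 5.4% | 47% vs 58% | 10.6 |

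A second log-rank simulation (4,000 runs, strata prevalences 50% and 35%, baseline hazard 0.03 per month) gave losses of 1.1, 4.8 and 13.3 points at 1.5, 2 and 3 per factor. When the strata carry no prognostic information, stratifying costs essentially nothing.

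**5. DOR.** Responders are selected after randomisation, so blocking no longer guarantees balance among them. Null simulation: 10,000 runs, no treatment effect on duration, 6 months, loss-of-response hazard 0.1 per month in the reference stratum, overall ORR 55% and 75% as in Section 8.1.
- Response unrelated to stratum: the unstratified test rejects 3.3% to 4.0%.
- Response assumed at 70% / 40% (intermediate / high risk) on control and 78% / 72% on ruxolitinib, which again averages 55% and 75%: the unstratified test rejects 5.5% to 6.4%.
- The stratified test stays between 5.0% and 5.3% in both settings.

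**The case against.** **OS, DFS, NRM and relapse already have models.** A reader might infer that treatment differences in these four endpoints are likely to be missed. The documents do not support that. Section 8.3.2 takes the reported difference from multivariable regression with both randomisation factors as candidates, and the Synopsis admits factors known to matter whatever their univariable P. What stands is narrow: neither passage requires the two factors to be included.

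**The protocol never says unstratified.** A SAP that is not shown could add the strata. That is fair. But the protocol does name these tests, and it writes stratified for ORR and not here, so as it stands the plain test is what it fixes.

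**The size is assumed.** No stratum hazard ratio, event rate or block size is given. It is tempting to argue a large effect from the 67% versus 30% week-4 resistance in Section 1.2. That figure compares high with low biomarker risk, whereas the trial enrols and stratifies intermediate versus high risk, and it measures response, not FFS or recurrence. It cannot size the loss.

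**Conservatism is not general.** A reader might infer that every secondary P-value is too large. For DOR that is not assured, as step 5 shows. The same caution would apply to recurrent acute GVHD if it were analysed among responders only; the Synopsis places all analyses on the intention-to-treat set.

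**A conservative test produces no excess of false positives, and these endpoints are secondary.** This is correct outside DOR, and it limits the severity.

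**Conclusion.** The point holds for FFS, DOR and recurrent acute GVHD: the randomisation factors are absent from the only between-arm test named for each.
- For FFS and recurrent acute GVHD the cost is power: 0 to 1 point if each factor has a hazard ratio of 1.5, about 4 to 5 points at 2, and 11 to 13 points only at 3. These figures rest on the assumptions in step 3 of the working, and the documents do not say where in this range the trial lies.
- For DOR the unstratified test can err in either direction, and using the strata still helps.
- For OS, DFS, NRM and relapse the effect is small; the remaining gap is that the selection rule does not guarantee inclusion of the two factors.

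This is a free improvement of modest severity.

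**What to change.** In Section 8.3.2 and the Synopsis:
1. Specify a log-rank test stratified by disease status and acute GVHD risk for FFS and DOR, and add FFS to Section 8.3.2.
2. Specify a stratified Gray test, or a Fine–Gray model containing both factors, for recurrent acute GVHD.
3. Force both factors into the existing Cox models (OS, DFS) and Fine–Gray models (NRM, relapse) regardless of univariable P, and stratify the accompanying log-rank and Gray tests. Keep those models as the single source of the reported treatment difference, so that no second estimate competes with them.

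The cost is a few sentences of wording. No new data are needed, because both factors are recorded at randomisation. With four strata and 198 patients, the simulations show essentially no power penalty even if the factors turn out not to be prognostic.

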### 8.3.3. Safety Analyses

A TEAE is either an AE reported for the first time or worsening of a pre-existing condition after first dose of study drug. Analysis of AEs will be limited to TEAEs, but data listings will include all AEs, regardless of their timing to study drug administration. Severity of AEs will be based on NCI CTCAE v4.0.

## 8.4. Handling of missing data

All randomized participants will be included in the primary analysis of all outcomes. The proportion of missing values on the primary and secondary outcomes would be <10%. Thus, a secondary analysis should be considered using multiple imputations and present best-case/worst-case scenarios if ignoring the missing data is not plausible.

## 8.5. Analyses for the Data Monitoring Committee

All data from the trial would be maintained confidential by the hospital’s data monitoring committee (DMC); also, it would help in data storage and analysis. The DMC of Chinese PLA General Hospital is composed of staffs in the clinical research center who will inspect the trial dataset. DMC is independent from the sponsor. The charter of DMC can be obtained from the clinical research center if necessary.

